**Table 6: Smoking abstinence rates by treatment groups from 2 weeks to 3, 6 and 12 months – Per protocol analysis**

| Outcome                                         | Intervention
N =
n (%) | Control
N =
n (%) | Odds ratio (95% CI) |
|-------------------------------------------------|------------------------------|-------------------------|---------------------|
| Smoking abstinence at 3-months           |                              |                         |                     |
| Self-reported prolonged abstinence              |                              |                         |                     |
| Self-reported 7-day point prevalence abstinence |                              |                         |                     |
| Smoking abstinence at 6-months           |                              |                         |                     |
| Biochemically verified prolonged abstinence     |                              |                         |                     |
| Self-reported prolonged abstinence              |                              |                         |                     |
| Self-reported 7-day point prevalence abstinence |                              |                         |                     |
| Smoking abstinence at 12-months          |                              |                         |                     |
| Biochemically verified prolonged abstinence     |                              |                         |                     |
| Self-reported prolonged abstinence              |                              |                         |                     |
| Self-reported 7-day point prevalence abstinence |                              |                         |                     |

Note: Deceased participants at each time-point will be excluded from those specific analyses.

Quitline sessions attended will be compared between the treatment groups using a  $\chi^2$  test.

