## 2. Aim and Objectives

This study aims to evaluate the effectiveness and safety of the combination of varenicline and NRT lozenges at assisting achievement of abstinence amongst heavy smokers admitted to six 'smoke-free' public hospitals in Australia.

The primary objective of the study is to compare biochemically-verified continuous abstinence in hospitalised smokers treated using varenicline plus NRT lozenge versus varenicline monotherapy.

The secondary objectives of this study are to compare:

- Self-reported 7-day point prevalence abstinence and continuous abstinence in the two treatment arms from 2 weeks to 3, 6 and 12 months after treatment initiation
- CO verified 7-day point prevalence abstinence at 6 and 12 months from treatment initiation for participants who self-report abstinence at these follow-ups
- Self-reported treatment adherence and adverse events to the study medicines at all follow-ups as well as the number of Quitline sessions attended after treatment initiation

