### 3.8.4 Follow-up 4: Six-months from treatment initiation

A RA (blinded to treatment allocation) will contact the participants at six months from hospital discharge. Participant self-reports of treatment adherence, adverse effects, withdrawal symptoms and cravings will be recorded. The number of Quitline calls made throughout the treatment period will also be recorded as well as the use of any other forms of behavioural/pharmacotherapy. Participants meeting the self-reported abstinence criteria (see 3.9.2) will be asked where they would like to take the CO breath test i.e. in hospital or by having a RA visit them at home.

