### 3.9.3 Secondary Outcome Measures

The secondary outcome measures are:

- Self-reported continuous abstinence from 2 weeks to three-, six- and twelve- months from treatment initiation
- CO verified continuous abstinence from 2 weeks to 12 months from treatment initiation for participants who self-report abstinence at this follow-up
- Self-reported 7-day point prevalence abstinence (i.e. smoking not even a puff in the past 7 days on the day of follow-up) measured from 2 weeks to 3, 6 and 12 months from treatment initiation
- CO verified 7-day point prevalence abstinence from 2 weeks to 6 and 12 months from treatment initiation for participants who self-report abstinence at these follow-ups
- Participant self-reports of withdrawal symptoms and cravings using the Mood and Physical Symptoms Scale (MPSS)
- Self-report of treatment adherence using the 8-item Tool for Adherence Behaviour Screening (TABS)
- Adverse events experienced from study medications
- Change in psychological distress
- Number of Quitline sessions attended/received
- Other health resources used including emergency department visits, GP visits (for smoking cessation), over-the-counter medicines used as well as the use of other smoking cessation therapies and alternate products

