### 4.2 Data Analysis

Data will be stored in a suitable database (e.g. REDCap™, ACCESS™) and exported for analysis in Statistical Package for Social Sciences (SPSS) (version 23.0; IBM, Armonk, NY) and Stata (ver 15, StataCorp, College Station, TX). As recommended by the Russell Standard, all randomised patients will be accounted for in the intention to treat (ITT) analysis. Participants with missing outcomes at follow-up or whose self-reported abstinence was not biochemically validated will be considered as smokers. Sensitivity analyses using multiple imputation methods will also be carried out. Deceased participants will be excluded from

analyses. In a supportive analysis of the primary efficacy endpoint, an analysis will also be conducted on the per protocol set, which excludes patients with any major protocol deviations.

Logistic regression analyses will be used to examine the efficacy of intervention on the primary outcome, after testing homogeneity between hospitals using a random effects meta-analysis. In the event of heterogeneity, a more robust model incorporating clustering by hospital will be fitted. The effect of intervention on continuous abstinence at 6 months will be tested in pre-specified subgroups (per hospital, nicotine dependence, highly motivated versus moderately motivated smokers and men versus women) using models fitted for each subgroup containing main effects for intervention and subgroup and an interaction between them. Statistical significance will be considered at a two-sided p value of 0.05.

All randomised participants who take at least one dose of the treatment medications will be included in the safety analysis. A chi-squared test will be done to compare the frequency of treatment withdrawal between the treatment and comparator arms. The number of participants discontinuing treatment prematurely for any reason will be summarised by treatment group and by reasons for discontinuation.

The incidence of all suspected adverse events will be summarised by treatment group under the following categories: type, severity, action taken and outcome. Severity of adverse events will be reported using the CTEAE grading scale (v5.0). The causality of the adverse events will be determined using the Noranjo algorithm.

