Deceased participants at each time-point will be excluded from those specific analyses. All analyses will be adjusted for baseline HSI score.

HSI and PHQ-9 score differences from baseline to 3, 6 and 12 months will be compared between the treatment groups using Mann-Whitney U tests.

**Table 3: Heaviness of Smoking Index and Patient Health Questionnaire-9 score differences from baseline to 3, 6 and 12 months**

| Outcome          | Baseline     |         | 3-months     |         | 6-months     |         | 12-months    |         |
|------------------|--------------|---------|--------------|---------|--------------|---------|--------------|---------|
|                  | Intervention | Control | Intervention | Control | Intervention | Control | Intervention | Control |
| HSI score |              |         |              |         |              |         |              |         |
| HSI score | ----         | ----    |              |         |              |         |              |         |

|                                                   |      |      |  |  |  |  |  |  |
|---------------------------------------------------|------|------|--|--|--|--|--|--|
| (% participants showing improvement) † |      |      |  |  |  |  |  |  |
| PHQ-9 score                                       |      |      |  |  |  |  |  |  |
| PHQ-9 score (% participants showing improvement)  | ---- | ---- |  |  |  |  |  |  |

860 \*Indicates significant differences ( $p < 0.05$ ) between the intervention and control groups. †Follow-up score  
861 lower than baseline score indicates improvement

862  
863  
864  
865  
866  
867

868 A data safety and monitoring board (DSMB) provided oversight of adverse event data on a  
869 periodic basis. For the primary safety outcome, the proportion of reported adverse events  
870 occurring between treatment initiation and over 12-month follow-up will be compared  
871 between the treatment groups using a  $\chi^2$  test or Mann-Whitney U tests, as appropriate.

872 **Table 4: Adverse events experienced by treatment group**

| Outcome                                                              | Intervention | Control | P-value |
|----------------------------------------------------------------------|--------------|---------|----------------|
| Adverse events experienced at week 1 * , n (%)            |              |         |                |

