**Table 7: Quitline sessions attended by treatment group**

| Outcome                                                         | Intervention | Control | P-value |
|-----------------------------------------------------------------|--------------|---------|----------------|
| Quitline session/s attended till Week 1*, n (%)                 |              |         |                |
| Quitline session/s attended till 3-months † , n (%)  |              |         |                |
| Quitline session/s attended till 6-months ‡ , n (%)  |              |         |                |
| Quitline session/s attended till 12-months § , n (%) |              |         |                |

Utilisation of other smoking cessation therapies and alternative products will be compared between the treatment groups using a  $\chi^2$  test.

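### The protocol's secondary outcome is the number of Quitline sessions, but the SAP plans no comparison of that number

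*Combined protocol and SAP*

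**What the plan says.** Protocol section 2 lists among the secondary comparisons "as well as the number of Quitline sessions attended after treatment initiation". Section 3.9.3 repeats it as an outcome measure: "Number of Quitline sessions attended/received". Both describe a count per participant. Section 3.8.4 provides for collecting one at six months: "The number of Quitline calls made throughout the treatment period will also be recorded".

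In the SAP, the sentence before Table 7 reads "Quitline sessions attended will be compared between the treatment groups using a" chi-squared test. The rows of Table 7 run from "Quitline session/s attended till Week 1" through "Quitline session/s attended till 3-months" to 6 and 12 months. Each is a single n (%) row with a P-value. Neither document plans a mean, median, rank test, rate ratio or count model for sessions.

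The same SAP treats adverse events more fully. It allows a chi-squared "test or Mann-Whitney U tests, as appropriate", and Table 4 has both n (%) and median/IQR rows at week 1, week 2, 3 months and 6 months.

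**The concern.** A chi-squared test on an n (%) row compares how many participants fall in a category, not how many sessions they had. On the natural reading of Table 7, a participant with one session and a participant with ten count the same. The trial would then report on whether Quitline was used, while its stated objective asks how much it was used.

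Quitline support is encouraged but optional (protocol section 3.6), so the amount of behavioural support received could differ between arms. That matters for describing what each arm actually received and for interpreting the abstinence result. A comparison of attendance alone can miss a difference in amount.

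**Working it through.** **Plan's own figure.** The documents give no power or sample size for Quitline sessions. The only figure is 160 per arm for abstinence (protocol section 4.1: 23% versus 38%, 80% power, two-sided 5%).

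- n = [1.960·√(2·0.305·0.695) + 0.842·√(0.23·0.77 + 0.38·0.62)]² / 0.15² = (1.276 + 0.541)² / 0.0225 ≈ 146.7, so 147 per arm.
- With continuity correction: (146.7/4)·[1 + √(1 + 4/(146.7·0.15))]² ≈ 159.8, so 160 per arm.

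The stated 160 is reproduced with the correction. It is used below as the number available per arm.

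**Inputs from the documents.** 160 per arm, 1:1 allocation (protocol section 3.3), and the protocol section 4.2 criterion: "Statistical significance will be considered at a two-sided p value of 0.05".

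**Assumed inputs.** Everything about the session distribution is assumed. Two families were used:

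- Negative binomial with mean μ and dispersion k, so P(at least one session) = 1 − (k/(k+μ))^k. The rate ratio between arms is 1.6.
- Hurdle: a proportion p uses Quitline at all, and each user has 1 + Poisson(m) sessions, so the mean among users is 1 + m.

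Each scenario had 4,000 simulated trials with complete session data. The simulation standard error is at most √(0.25/4000) = 0.8 percentage points. Three tests were compared: uncorrected chi-squared on at least one session versus none, Mann-Whitney on the count, and a large-sample z-test of mean counts.

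**Hand check of two chi-squared entries.**

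- Negative binomial, μ = 1 versus 1.6, k = 1: attendance is 1 − 1/2 = 0.500 versus 1 − 1/2.6 = 0.615, a difference of 0.115. The null SE is √(2·0.558·0.442/160) = 0.0555 and the alternative SE is √((0.250 + 0.237)/160) = 0.0552. Power = Φ[(0.1154 − 1.96·0.0555)/0.0552] = Φ(0.12) ≈ 55%. Simulated: 55.1%.
- Uptake only, 30% versus 45%: power = Φ[(0.15 − 1.96·0.0541)/0.0535] = Φ(0.82) ≈ 79%. Simulated: 79.5%.

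**Results (power, %).**

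| Assumed scenario | Any session, % | Chi-squared | Mann-Whitney | Test of means |
|---|---|---|---|---|
| NB, μ 1, k 0.3 | 36 v 43 | 23.9 | 34.7 | 51.4 |
| NB, μ 1, k 0.5 | 42 v 51 | 36.0 | 53.8 | 70.1 |
| NB, μ 1, k 1 | 50 v 62 | 55.1 | 78.2 | 87.5 |
| NB, μ 2, k 0.5 | 55 v 63 | 29.7 | 57.1 | 75.9 |
| NB, μ 2, k 1 | 67 v 76 | 47.2 | 87.1 | 94.2 |
| NB, μ 3, k 1 | 75 v 83 | 38.5 | 89.3 | 96.0 |
| NB, μ 3, k 2 | 84 v 91 | 50.9 | 99.3 | 99.7 |
| Same uptake, users average 2 v 4 | 50 v 50 | 5.7 | 80.3 | 99.8 |
| Same uptake, users average 2 v 3 | 70 v 70 | 5.1 | 91.0 | 98.3 |
| Same uptake, users average 2 v 4 | 30 v 30 | 5.0 | 21.0 | 91.5 |
| Both differ, users average 2 v 3 | 30 v 40 | 48.0 | 79.8 | 97.2 |
| Uptake only, users average 3 v 3 | 30 v 45 | 79.5 | 76.8 | 66.9 |
| Uptake only, users average 3 v 3 | 50 v 65 | 77.4 | 68.7 | 60.9 |
| No difference, users average 3 v 3 | 50 v 50 | 5.6 | 4.9 | 5.0 |

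When the arms differ in sessions per person, the count tests do better in every scenario. When only sessions per user differ, chi-squared has no power beyond its error rate. When only uptake differs, chi-squared is the best of the three. Mann-Whitney is itself weak (21%) when few participants use Quitline and uptake is equal, because most values are tied at zero.

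**The case against.** Four points can be made for the plan.

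1. A reader might infer that chi-squared loses power here in general. The documents do not support that. They give no session distribution, and Quitline is optional, so a pure difference in uptake is plausible. In that case chi-squared is equal or slightly better. This stands, and the power argument is conditional.
2. A reader might take the SAP to state an any-versus-none comparison. It does not. That reading is inferred from the single n (%) row, the session/s label and the choice of test. The footnote markers in Table 7 have no visible text, so a definition there cannot be ruled out. This stands as a caution, but no other reading fits the table shell better, and no count summary appears anywhere.
3. A reader might assume the count is collected throughout. Only the six-month section says a number is recorded, and it refers to calls over the treatment period. Section 3.8.5 mentions only use of the service at 12 months, and the sections on the first three follow-ups do not mention Quitline. Participants recruited before the 12-month visit was added have it only if they consent. This stands and limits what can be promised at 12 months.
4. A reader might fear bias in the abstinence comparison. Quitline use arises after randomisation, is offered on the same terms in both arms, and is not a term in the planned abstinence models. A difference in use would help explain an effect, not bias the intention-to-treat estimate. This stands.

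None of the four removes the mismatch between a count outcome and an analysis that does not use the count.

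**Conclusion.** The point holds as a mismatch between protocol and SAP: the number of sessions is a stated secondary objective and outcome, and no comparison of that number is planned. This does not depend on any power assumption. It is also out of line with how the SAP handles adverse events.

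The power consequence is conditional on assumed distributions, 160 per arm and complete session data. At a rate ratio of 1.6, chi-squared on attendance has about 24-55% power against 35-99% for Mann-Whitney. With equal uptake it has 5-6%, against 80% for Mann-Whitney in the central case (50% users, averaging 2 versus 4 sessions) and 21-91% across the three cases tried. With a difference in uptake only, it has 77-80% against 69-77%, so nothing is lost.

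The point is minor. The sample size rests on abstinence alone, and neither the primary efficacy conclusion nor the safety conclusion depends on this test.

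**What to change.** In the SAP:

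- Add median (IQR) rows for the session count to Table 7.
- Compare the cumulative count to 6 months by Mann-Whitney U, as the SAP already allows for adverse events. A negative binomial rate ratio with 95% CI is a reasonable alternative. It gives an effect size, and it deserves consideration if many participants are expected to have no sessions.
- Do the same at 12 months if the follow-up form records a number. Confirm this first, and confirm that the six-month count covers the whole period from treatment initiation.
- Keep the n (%) rows and their chi-squared test as a supplement, and label them explicitly as at least one session.
- State the denominator and how missing session counts are handled. The rule that treats missing participants as smokers does not cover this outcome.

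The cost is a few lines of SAP text and some table rows. At six months no new data are needed, given the planned record of calls. At 12 months the cost depends on what the form collects.

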**Table 7: Quitline sessions attended by treatment group**

| Outcome                                                         | Intervention | Control | P-value |
|-----------------------------------------------------------------|--------------|---------|----------------|
| Quitline session/s attended till Week 1*, n (%)                 |              |         |                |
| Quitline session/s attended till 3-months † , n (%)  |              |         |                |
| Quitline session/s attended till 6-months ‡ , n (%)  |              |         |                |
| Quitline session/s attended till 12-months § , n (%) |              |         |                |

Utilisation of other smoking cessation therapies and alternative products will be compared between the treatment groups using a  $\chi^2$  test.

**Table 8: Self-reported utilisation of other smoking cessation therapies and alternative products**

| Treatments                      | Intervention | Control | P-value |
|---------------------------------|--------------|---------|----------------|
| 3-months follow-up       |              |         |                |
| Nicotine replacement therapy    |              |         |                |
| Bupropion                       |              |         |                |
| Non-pharmacological assistance* |              |         |                |
| 6-months follow-up       |              |         |                |
| Nicotine replacement therapy    |              |         |                |
| Bupropion                       |              |         |                |
| Non-pharmacological assistance* |              |         |                |
| 12-months follow-up      |              |         |                |
| Nicotine replacement therapy    |              |         |                |
| Bupropion                       |              |         |                |
| Non-pharmacological assistance* |              |         |                |

\*Non-pharmacological assistance includes acupuncture, hypnotherapy, quit smoking group, etc.
